##### Motivational variables

To assess for motivational variables, we will gather participants’ self-reported information as outlined below.

1. *TPB variables*: Behavioral intentions, attitudes toward behaviors, perceived norms, perceived behavioral control, behavioral beliefs, normative beliefs and control beliefs will be measured according to the TPB recommendations
[24]. The questionnaire was tested in a previous study and showed good psychometric properties ([name], unpublished manuscript). These measures will allow us to identify the predictors of behavioral intentions and consequently to modify or strengthen the beliefs upon which they are based during the motivational interventions.

2. *Fear of movement*: We will use the total score on the Spanish adaptation of the Tampa Scale for Kinesiophobia to measure fear of movement
[53]. Patients will rate 11 items on a four-point Likert scale (from 1 = totally disagree to 4 = totally agree). This measure will allow us to explore the role of fear of movement in relation to behavioral intentions.

##### Health status variables

To assess for health status variables, we will gather participants’ self-reported information as outlined below.

1. *Pain*: We will use the total score on an 11-point numerical rating scale (from 0 = “no pain at all” to 10 = “the worst pain you can imagine”) adapted from Jensen *et al*.
[54] to assess the maximum, minimum and usual pain intensity during the week prior to the evaluation and the pain intensity that moment. The scale has shown good psychometric properties in Spanish FM samples
[55,56].

2. *FM impact*: We will use the total score of the consensus version of the Spanish adaptation of the Fibromyalgia Impact Questionnaire (FIQ), which is valid and reliable
[57].

3. *Emotional status*: The perceived total distress is measured with the Spanish adaptation
[58] of the Hospital Anxiety and Depression Scale
[59]. Patients rate 14 items on a four-point answer scale. This scale has been shown to be valid and reliable
[58].

Our aim in assessing these variables is, on the one hand, to explore their role in behavioral intention and, on the other hand, to explore them as potential confounders.

#### Phase II (second and third years)

A summary of variables and the schedule of phase II is given in Table 
3.

**Table 3 T3:** **Measures and schedule of phase II**^
**a**
^

	**Instrument**	**Schedule**			
**Outcomes**		**Baseline**	**Week 7**	**Week 20 (3 months)**	**Week 43 (9 months)**
*Primary*					
Walking pattern	*Ad hoc* self-report scale	X	X	X	X
	Daily logs		X	X	X
Steps and distance	Pedometer^b^		X	X	X
*Secondary*					
Total physical activity	IPAQ	X	X	X	X
Intense physical activity		X	X	X	X
Moderate physical activity		X	X	X	X
Walking		X	X	X	X
Sitting		X	X	X	X
Physical function	Six-Minute Walk Test	X	X	X	X
FM Impact	FIQ	X	X	X	X
Pain intensity	*Ad hoc* scale	X	X	X	X
Emotional status: Distress	HADS	X	X	X	X
*Mediators*					
Behavioral intention^c^	TPB items	X	X	X	X
Implementation intentions^c^	*Ad hoc* items		X	X	X

^a^FIQ: Fibromyalgia Impact Questionnaire; HADS: Hospital Anxiety and Depression Scale; IPAQ: International Physical Activity Questionnaire; TPB: Theory of Planned Behavior. ^b^Limit of recording is 60 days. ^c^Also measured at the end of the intervention sessions.

#### Primary outcome measures

Two primary outcomes will be assessed as indicators of each intervention’s effect on exercise adherence:

1. We will measure the proportion of participants who perform the full minimum walking criteria (at least 30 minutes in bouts of 15 minutes with a small rest between bouts, twice times weekly over a minimum of 6 consecutive weeks) at the end of the 6-week period and the proportion of participants who have maintained it at 3 and 9 months. The expected efficacy of MIG is 30% higher than CG and 10% higher than IG.

2. Among participants who perform the full minimum walking criteria, we will focus on the proportion who reach the recommended pattern for FM patients at week 6 (between two and four times weekly for about 50 minutes in bouts of 15 to 20 minutes over a minimum of 6 consecutive weeks)
[31].

We will use the same self-reported measurements of the behavior from phase I (*ad hoc* self-reported items and daily logs) and pedometer readings.

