[31]. We chose this pattern because it includes several components which will encourage FM patients to do unsupervised physical exercise. Walking is an accessible, cheap and flexible activity; it includes resting; and it requires minimal time, which aids habit acquisition. Although we selected this pattern, we reduced the minimum daily time to 30 minutes (in two bouts of 15 minutes each) and at least two times weekly because our target population is sedentary. In addition, patients will be advised to start physical exercise gradually
[10,11], beginning with a low, comfortable intensity according to differences in physical capacity
[4]. It is well known that FM patients can benefit from low-intensity walking programs 2 or 3 days per week
[32]. Moreover, 30 minutes of continued physical activity has also been shown to have positive effects on health in the general population
[33].

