### Interventions

In previous studies in the reviewed literature, we found that interventions for the promotion of walking have been heterogeneous and that no single method has proved to be more effective than others
[33]. One of the main advantages of our study is that the intervention is based on two well-established theories for predicting behavior. Following the procedures described in previous research
[42,43], all participants will receive information about the benefits of physical exercise in relation to their FM, and they will be asked to engage in the selected walking criteria. In addition, MIG participants will receive motivational interventions, and both the MIG and IG groups will receive information on the positive effects of making plans, specifying (1) days, (2) specific times of day, (3) location (for example, close to work, around the neighborhood) and (4) duration of the exercise (starting from the established minimum). Thus, they will be requested to write a specific individualized plan. The estimated duration of the intervention in each group is 90 minutes, conducted in only one group session with a maximum of 10 people. Figure 
2 shows the schedule for the intervention day.

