## Discussion

The benefits of physical activity associated with FM patients’ health status are well established. Exercise programs have been applied in isolation or together with other interventions in multidisciplinary treatments. There is evidence of clinical benefits of aerobic exercise for FM patients
[3]. Most exercise programs are supervised in professional contexts, but the reported adherence to these programs is not encouraging
[8-12]. Walking represents a similar problem. Although some authors have reported satisfactory compliance rates for walking
[14], the exercise was performed in specific conditions, with walking poles and in group sessions with a monitor, which might contribute to an increase in adherence.

Walking is recommended to people with FM
[4] and to adults in general
[62]. It is easily accessible, cheap and popular, and it helps promote self-regulation and self-efficacy
[10]. Our study will endorse these features because, although unsupervised, participants will be expected to walk for a minimum time under specific conditions. This minimum is easily reached by sedentary FM participants, and each participant can increase it gradually (at least up to the recommended pattern for FM patients
[31]) or maintain the minimum level established in the study. In fact, because our intervention promotes participants’ self-regulation, we also expect that they will set their own goals, which may include longer walking times. In addition, the study will allow us to test whether different basal walking patterns have differential benefits by analyzing the effect modifier of the relationship between experimental conditions and main results. For example, the effect of interventions might be higher in participants who do not walk at all than in participants who do.

To the best of our knowledge, this study is the first to address adherence to unsupervised walking patterns of FM patients by combining motivational and volitional strategies with strong theoretical foundations in health psychology. This combination has shown good results in the general population
[16,18,19], but to our knowledge it has not been used in FM patients.

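### The second primary outcome is computed only among women who succeeded on the first, so its between-arm comparison is not randomised and can make an effective arm look worse

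*Protocol article*

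**What the plan says.** Under Primary outcome measures, the protocol article states: "Two primary outcomes will be assessed as indicators of each intervention’s effect on exercise adherence". The first outcome is the proportion meeting the minimum walking criteria. The second reads: "Among participants who perform the full minimum walking criteria, we will focus on the proportion who reach the recommended pattern for FM patients". It is judged at week 6, and the pattern to be reached is "between two and four times weekly for about 50 minutes in bouts of 15 to 20 minutes over a minimum of 6 consecutive weeks".

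Under Sample size calculation, the expected increases in prevalence from baseline are 10% for CG, 20% for IG and 40% for MIG, with 115 women per group. No effect size or sample size is given for the second outcome.

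On how women begin, the Description of the overall project says that "we reduced the minimum daily time to 30 minutes (in two bouts of 15 minutes each) and at least two times weekly" and that "patients will be advised to start physical exercise gradually". Under Interventions, the written plans made in MIG and IG specify "duration of the exercise (starting from the established minimum". The Discussion says that "each participant can increase it gradually (at least up to the recommended pattern for FM patients", that a woman may also stay at the minimum, and that "we also expect that they will set their own goals, which may include longer walking times".

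**The concern.** An effect of an allocated intervention is protected by randomisation when the arms are compared as randomised. Here each arm is first cut down to its responders. CG responders are women who walk after information alone. MIG responders are women of that kind plus those whom planning and motivation brought in. If the added women reach the recommended pattern less often, the MIG proportion falls because MIG succeeded on the first outcome. A measure labelled primary could then report a benefit as a deficit.

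The timing raises a smaller issue. A run of at least six weeks at the recommended level, judged at week 6, leaves no time for build-up, while other parts of the article describe building up from a lower start.

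**Working it through.** **Plan's own figure.** There is none for the second outcome. The 115 per group belongs to the first outcome. Standard two-proportion formulas (two-sided 5%, 80% power) give 199, 32 and 82 per arm for 10% v 20%, 10% v 40% and 20% v 40%, so 115 is not reproduced. That is a separate matter, and 115 is taken as stated here.

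**Expected denominators.** The stated increases are read as success proportions, since eligible women do not meet the pattern at entry. Denominator = women in arm × expected success (10%, 20%, 40%).

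| Women per arm (CG / IG / MIG) | CG | IG | MIG |
|---|---|---|---|
| 115 each (Sample size calculation) | 11.5 | 23 | 46 |
| 154 / 153 / 142 (Table 1) | 15.4 | 30.6 | 56.8 |
| 274/3 = 91.3 each (274 attended; equal split assumed) | 9.1 | 18.3 | 36.5 |

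**Direction of the comparison (assumed rates).** If 5% of all CG women and 12% of all MIG women reach the recommended pattern, the proportions among responders are 5/10 = 50% and 12/40 = 30%. MIG is better by 7 points in all women and worse by 20 points among responders.

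**Why this happens.** Assume that 10% of women in every arm would meet the minimum anyway and that a share r of them reaches the recommended pattern, whatever the arm. The intervention adds e = 0, 10 or 30 points of further women (CG, IG, MIG), of whom a share s reaches the pattern. Nobody is deterred.

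- All randomised: 0.10·r + e·s
- Among responders: (0.10·r + e·s) / (0.10 + e)

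With r = 0.5:

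| s | All randomised, CG / IG / MIG | Among responders, CG / IG / MIG |
|---|---|---|
| 0 | 5% / 5% / 5% | 50% / 25% / 12.5% |
| 0.1 | 5% / 6% / 8% | 50% / 30% / 20% |
| 0.2 | 5% / 7% / 11% | 50% / 35% / 27.5% |

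The 5% v 12% example corresponds to s = (12 − 5)/30 = 23%. In this model MIG is truly better whenever s > 0 and looks worse whenever s < r.

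**Precision.** With subsets from 115 per arm, and assuming 30% v 50% among responders, power is 21% for MIG v CG and 35% for MIG v IG (two-sided 5%). At a common proportion of 0.5, the 95% half-width for MIG − CG is 1.96·√(0.25/11.5 + 0.25/46) = 32 points among responders. With 115 per arm it is 1.96·√(0.5/115) = 13 points.

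**Timing.** A woman at 30 minutes in week 1 who first reaches about 50 minutes in week k has 7 − k qualifying weeks at week 6: five if k = 2, four if k = 3. She completes six at week k + 5, so at week 7 at the earliest. Only k = 1 qualifies at week 6.

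**The case against.** The strongest reply is that the trial's main conclusion does not rest on this outcome. The main hypothesis and the sample size concern the first outcome, and the Phase II analysis text speaks of one main outcome. No effect is postulated for the second. That stands as a limit on the consequences, but it does not answer the defect: the article still calls the measure primary and an indicator of effect.

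The rates behind the reversal are assumptions. They show that reversal is possible and by what route, not that it is likely. The denominators for 274 women may also change, since the article plans to contact a further 180.

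Several stronger readings are tempting, and the documents do not support them:

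- A reader might infer that the week-6 rule drives the outcome toward zero in every arm. The instruction on plan duration can be read as a floor, and longer goals are allowed. It is given only to MIG and IG. The general advice on a gradual start is explained as low, comfortable intensity, not as 30 minutes. Participants already report a median of 180.5 minutes of walking per week (Table 5); this covers all walking, so it does not show compliance with the pattern, but it gives no support to a near-zero rate.
- A reader might infer that a woman walking more than four times weekly is scored a failure, against the Discussion. The Discussion speaks of longer times, not more sessions, and its wording is that of a threshold to be reached.
- A reader might expect a large gain in precision from the wider denominator. In the 5% v 12% example with 115 per arm, the half-width is 1.96·√((0.12·0.88 + 0.05·0.95)/115) = 7.2 points around a difference of 7. The gain is validity first.

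**Conclusion.** The definition is wrong as written for its stated purpose. The second primary outcome conditions on a response that the plan itself expects to differ fourfold between CG and MIG, so it does not estimate an effect of allocation, and it can point the wrong way. The expected subsets are about 11.5, 23 and 46 women at 115 per arm, given the plan's own 10%, 20% and 40%. The size of any reversal depends on assumed rates; its possibility requires only that women brought in by the intervention reach the recommended pattern less often than those who would have walked anyway.

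The timing point is narrower. The outcome is closed to a woman who starts at the 30-minute minimum and builds up, and open to one who walks about 50 minutes from week 1. It is an inconsistency to be reconciled, not evidence that the outcome is unattainable.

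**What to change.** Define the second outcome in all randomised women of each arm: reached the recommended pattern, yes or no. Alternatively, use one ordered outcome in all randomised women with the levels below minimum, minimum and recommended. Report the proportion among responders as description only, without a between-arm test or causal wording.

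Reconcile the Description of the overall project, Interventions, Primary outcome measures and Discussion on whether the six consecutive weeks at the recommended pattern must run from week 1, and on how that fits a start at the minimum with gradual increase. This concerns the outcome definition; the walking recommendation itself is not changed.

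The denominator change is one of wording and needs no new data. Its downside is smaller reported proportions, for example 5% and 12% in place of 50% and 30%. Moving the assessment to later visits or ranking the outcome as secondary is open to debate and is not needed to remove the bias.

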#### Secondary outcome measures

*Six-Minute Walk Test (6MWT)*: The 6MWT is a clinically relevant measure of the physical function that the Spanish Society of Rheumatology recommends using with FM patients
[60].

The remaining secondary measures are described in the measures of phase I: IPAQ-S score
[49], FIQ score
[57], pain intensity rating
[55] and emotional status
[58].

#### Mediators

1. *Behavioral intentions*: In a previous study, we designed and proved the high internal consistency (α = 0.87) of five items for an *ad hoc* questionnaire ([name], unpublished manuscript). These items are used to assess the individual’s readiness to carry out the full walking pattern: “I intend to walk,” “I will walk,” “I am willing to walk,” “I plan to walk” and “I will make an effort to walk at least 30 minutes in bouts of 15 minutes, with a small rest between bouts, twice weekly for a minimum of 6 consecutive weeks.” All answers given are scored according to a numerical rating scale from 1 to 7.

2. *Implementation intentions*: A postexperiment questionnaire will be used to assess how committed patients felt toward meeting their goals (“How committed did you feel to the self-regulation intention?” and “How much did you try to achieve your self-regulation intentions?”) and their perceived performance (“How difficult was it to achieve your walking behavior?” “Did your self-regulation intention help you achieve the proposed walking behavior?” and “How well did you succeed in realizing your self-regulation intention?”). All of these items will be accompanied by 11-point answer scales ranging from 0 (“not at all”) to 10 (“very”).

#### Statistical analysis

Data will be entered into a relational database system (Microsoft Access; Microsoft, Redmond, WA, USA) with range rules and forms, which will reduce the number of data entry mistakes. In addition, we will apply a program to check and clean data
[61]. Analyses will be made using the IBM SPSS Statistics 21 software package (SPSS, Chicago, IL, USA) and LISREL software (SSI Scientific Software International, Skokie, IL, USA).

#### Phase I

Descriptive analyses have been performed. The sociodemographic characteristics, symptoms, walking and physical activity of eligible and noneligible populations have been compared by conducting χ^2^ tests, *t*-tests, analysis of variance and median nonparametric tests, depending on the characteristics of the variables (Table 
4). These comparisons were conducted to ensure that both samples differ only with regard to the inclusion criteria of the study. The same analyses were performed to compare participants with individuals who refused to participate and nonresponders (that is, not contacted or not available at the time of measurement) (Table 
5).

**Table 4 T4:** **Descriptive statistics in eligible and noneligible populations**^
**a**
^

**Variables**	**Noneligible**					**Eligible**				
	**Mean**	**(95% CI)**	**SD**	**Median**	**(95% CI)**	**Mean**	**(95% CI)**	**SD**	**Median**	**(95% CI)**
Age (years)	53.51	(52.59 to 54.42)	8.52	54.24		52.14	(51.41 to 52.87)	8.96	52.91	
Pain intensity	6.63	(6.43 to 6.83)	1.82	6.62		6.73	(6.59 to 6.87)	1.70	6.75	
Fatigue	8.01	(7.79 to 8.23)	2.01	8.00		8.20	(8.36 to 8.39)	1.96	9.00	
Fatigue upon waking	7.99	(7.74 to 8.25)	2.37	9.00		8.17	(8.00 to 8.25)	2.20	9.00	
Fatigue impact perception	6.78	(6.48 to 7.08)	2.77	7.00		7.01	(6.78 to 7.23)	2.72	7.00	
Cognitive problems	6.77	(6.48 to 7.05)	2.62	7.00		7.00	(6.78 to 7.21)	2.66	8.00	
Sleeping disorder impact perception	7.07	(6.75 to 7.38)	2.94	8.00		7.02	(6.70 to 7.26)	2.95	8.00	
Cognitive problems impact perception	6.30	(6.00 to 6.61)	2.83	7.00		6.57	(6.34 to 6.80)	2.83	7.00	
IPAQ-Sitting, mi/wk				240.5	(240.5 to 300.5)				300.5	(240.5 to 300.5)
IPAQ-Walking, min/wk				300.5	(245.5 to 350.5)				180.5	(140.5 to 180.5)
IPAQ-Moderate activities, min/wk				0.5	(0.5 to 60.5)				0.5	(0.5 to 0.5)
IPAQ-Vigorous activities, min/wk				0.5	(0.5 to 0.5)				0.5	(0.5 to 0.5)
IPAQ-Total activities, min/wk				383.5	(300.5 to 420.5)				180.5	(150.5 to 210.5)
	** *n* **	**(%)**				** *n* **	**(%)**			
Education level										
Literate	42	(12.5)				67	(11.5)			
Primary	138	(40.9)				261	(44.8)			
Secondary	106	(31.5)				163	(28.0)			
University	51	(15.1)				91	(15.6)			
Employment status										
Working	88	(26.3)				177	(30.5)			
Unemployed	63	(18.8)				118	(20.4)			
Retired	26	(7.8)				38	(6.6)			
Retired (pain)	39	(11.6)				59	(10.2)			
Sick leave	32	(9.6)				50	(8.6)			
Housewife	87	(26.0)				138	(23.8)			

^a^CI: Confidence interval; IPAQ: International Physical Activity Questionnaire; SD: Standard deviation.

**Table 5 T5:** **Descriptive statistics in participants and nonparticipants from eligible population**^
**a**
^

**Variables**	**Nonparticipant group**					**Participant group**				
	**Mean**	**(95% CI)**	**SD**	**Median**	**(95% CI)**	**Mean**	**(95% CI)**	**SD**	**Median**	**(95% CI)**
Age (years)	52.41	(51.42 to 53.40)	8.79	53.17		51.84	(50.75 to 52.93)	9.16	52.69	
Pain intensity	6.76	(6.56 to 6.95)	1.72	6.75		6.70	(6.50 to 6.90)	1.67	6.50	
Fatigue	8.19	(7.96 to 8.42)	2.02	9.00		8.22	(7.99 to 8.44)	1.90	9.00	
Fatigue upon waking	8.24	(7.99 to 8.49)	2.22	9.00		8.10	(7.84 to 8.36)	2.17	9.00	
Fatigue impact perception	7.05	(6.76 to 7.34)	2.60	8.00		6.96	(6.62 to 7.29)	2.85	7.00	
Cognitive problems	6.92	(6.62 to 7.22)	2.69	7.00		7.08	(6.77 to 7.39)	2.63	8.00	
Sleep disorder impact perception	7.01	(6.66 to 7.35)	3.07	8.00		7.03	(6.70 to 7.37)	2.82	8.00	
Cognitive problems impact perception	6.46	(6.14 to 6.79)	2.86	7.00		6.68	(6.35 to 7.02)	2.79	7.00	
IPAQ-Sitting, min/wk				270.5	(240.5 to 300.5)				300.5	(240.5 to 330.5)
IPAQ-Walking, min/wk				150.5	(120.5 to 200.5)				180.5	(120.5 to 210.5)
IPAQ-Moderate activities, min/wk				0.5	(0.5 to 0.5)				0.5	(0.5 to 15.5)
IPAQ-Vigorous activities, min/wk				0.5	(0.5 to 0.5)				0.5	(0.5 to 0.5)
IPAQ-Total activities, min/wk				160.5	(120.5 to 210.5)				210.5	(180.5 to 240.5)
	** *n* **	**(%)**				**n**	**(%)**			
Education level										
Literate	32	(10.4)				35	(12.8)			
Primary	132	(42.9)				129	(47.1)			
Secondary	86	(27.9)				77	(28.1)			
University	58	(18.8)				33	(12)			
Employment status										
Working	92	(30.4)				85	(31.1)			
Unemployed	59	(18.9)				59	(21.6)			
Retired	25	(8.1)				13	(4.8)			
Retired (pain)	32	(10.4)				27	(9.9)			
Sick leave	32	(10.4)				18	(6.6)			
Housewife	67	(21.8)				71	(26.0)			

^a^CI: Confidence interval; IPAQ: International Physical Activity Questionnaire; SD: Standard deviation.

No significant differences were found between the noneligible population (*n* = 338) and the eligible population (*n* = 582) regarding the distribution of the patients drawn from the different FM associations (χ^2^ = 2,670, *P* = 0.445, df = 3. With regard to sociodemographic variables, we found significant differences only for age between the eligible and the noneligible populations (*t* = 2.264, *P* = 0.024, df = 914, mean difference = 1.37, 95% CI = 0.18 to 2.55). This difference was not found, however, when we considered the FM associations in the analysis (eligible group by FM association: F = 1.928, *P* = 0.124; noneligible group by FM association: F = 2.403, *P* = 0.067). No significant differences were found between groups for either education level (χ^2^ = 1.810, *P* = 0.613, df = 3) or employment status (χ^2^ = 5.912, *P* = 0.436, df = 6). Groups were also similar in pain intensity perception (*t* = -0.833, *P* = 0.415, df = 913), fatigue (*t* = -1.38, *P* = 0.167, df = 909), fatigue upon waking (*t* = -1.16, *P* = 0.245, df = 910), impact perception of fatigue (*t* = -1.21, *P* = 0.226, df = 909), cognitive problems (*t* = -1.27, *P* = 0.205, df = 910), impact perception of cognitive problems (*t* = -1.37, *P* = 0.173, df = 908) and impact perception of sleeping disorders (*t* = 0.25, *P* = 0.806, df = 911). The last six variables were included in the mailed questionnaire to identify the study population. All of them were calculated for the previous week and were measured using an 11-point numerical rating scale (from 0 = nothing at all to 10 = totally). In relation to IPAQ-S variables, median total activity, walking and moderate-intensity activities were different (*P* ≤ 0.01) and similar in vigorous activities (*P* = 0.296) and sitting (*P* = 0.442) (Table 
4).

All eligible individuals were contacted (*N* = 582) because of the difficulties involved in the participation of the first 449 selected women, such as the failure to contact them after repeated attempts, nonattendance after three citations and distance of residence from the study location. Ultimately, 274 patients accepted and attended the first evaluation session (participation rate = 47.1%). No significant differences were found between these 274 participants and women with FM who did not participate in this phase of the study (*n* = 308) on the basis of any of the above-mentioned variables (age: *t* = 0.767, *P* = 0.443, df = 579; education level: χ^2^ = 5.567, *P* = 0.135; df = 3; employment status: χ^2^ = 7.567, *P* = 0.272, df = 6; pain intensity perception: *t* = 0.389, *P* = 0.697, df = 579; fatigue: *t* = -0.178; *P* = 0.858, df = 576; fatigue upon waking: *t* = 0.785, *P* = 0.433, df = 576; impact perception of fatigue: *t* = 0.410, *P* = 0.410, df = 577; cognitive problems: *t* = -0.718, *P* = 0.473, df = 577; impact perception of cognitive problems: *t* = -0.939, *P* = 0.348, df = 577; impact perception of sleeping disorders: *t* = -0.107, *P* = 0.915, df = 577). The groups showed different medians of moderate activities (*P* ≤ 0.01), but similar medians in total activity (*P* = 0.066), sitting (*P* = 0.208), walking (*P* = 0.609) and vigorous activities (*P* = 0.115). In addition, the groups presented a proportion of noncompliance similar to that of the total unsupervised pattern (45.8% and 44.2%, respectively) and the same proportion reported for medical recommendation to walk (81.8% in each group) (Table 
5).

Internal consistency analysis will be performed for the different scales using the Cronbach’s α coefficient. Path analysis will be conducted to identify the relative weights of attitudes, perceived norms and perceived behavioral control in the prediction of the behavioral intention (path coefficients). Furthermore, we will test the role of the fear of movement, pain and FM impact. Spearman and Pearson correlations and cross-tabulation analysis (depending on the variables) will be used to explore the agreement of the behavioral measurements.

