### Description of the overall project

The study consists of two phases, both based on the same population.

Phase I, conducted over the course of 1 year, is a cross-sectional study with two measurement stages and the following three aims:

1. We will seek to gain access to the reference population, identify the eligible population, select the study population and identify the prevalence of our selected walking criteria (stage 1). The results of stage 1 are included in this paper.

2. We will seek to identify the predictors of the behavioral intention to carry out the selected walking program using the TPB and exploring the role of pain, impact of FM and fear of movement (stage 2).

3. We will seek to explore the concordance of walking behavior measurements (subjective and objective measures) (stage 2).

Phase II, which will be conducted over the course of 2 years, is an experimental, randomized, triple-blind study with two treatment groups and one active control group. Longitudinal measures will be taken at baseline and at 7 weeks, 3 months and 9 months of postexperimental intervention. One group will receive a motivational plus implementation intentions intervention (MIG), a second group will receive only an implementation intention intervention (IG) and the control group (CG) will be given a neutral task related to postural hygiene. The three groups will receive the same information on the benefits of physical exercise in FM. Motivational intervention will be based on the predictors of behavioral intention as measured and identified in phase I (stage 2) in order to create or strengthen the behavioral intention during the experimental study.

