Third, we have designed weekly and daily logs to assess walking behavior over the course of 6 consecutive weeks. Daily logs include the days and minutes of walking and the duration of rest during the activity. In addition, participants score the perceived intensity of the activity using the Borg Rating of Perceived Exertion scale
[52]. Participants will use a pedometer (3D USB Pedometer PDM-2608) to record the number of steps and distance covered over the same period.

These measures will be used to explore the agreement between subjective and objective measurements. We need to establish this agreement because the entire study population will use daily logs, but only half of them will use pedometers.

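### For continuous walking measures, agreement is judged only by correlations, which cannot show systematic over-reporting; for the planned cross-tabulations no agreement or asymmetry statistic is named

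*Protocol article*

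**What the plan says.** In the protocol article, the third aim of Phase I (Description of the overall project) is to "explore the concordance of walking behavior measurements (subjective and objective measures". The Behavioral variables section repeats the purpose, "These measures will be used to explore the agreement between subjective and objective measurements", and gives the reason: "We need to establish this agreement because the entire study population will use daily logs, but only half of them will use pedometers".

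The method is in Statistical analysis, Phase I: "Spearman and Pearson correlations and cross-tabulation analysis (depending on the variables) will be used to explore the agreement of the behavioral measurements". No estimate of bias, limits of agreement, concordance or intraclass coefficient, kappa or acceptance threshold is named.

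The instruments do not share a unit. For the logs, "Daily logs include the days and minutes of walking and the duration of rest during the activity"; the pedometer is used "to record the number of steps and distance covered over the same period". The ad hoc scale asks for minutes per day, days per week and consecutive weeks.

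The first primary outcome of Phase II is a threshold on walking: "at least 30 minutes in bouts of 15 minutes with a small rest between bouts, twice times weekly", kept up for at least six consecutive weeks. It draws on the same self-report items and logs, together with pedometer readings.

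**The concern.** Agreement asks whether two measures give the same answer; correlation asks whether they rank or scale women alike. A log can rank women almost perfectly and still be too high for nearly all of them. Self-reported exercise invites exactly that error, and for the half of the women without a pedometer nothing else checks the log.

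This matters because the primary outcome is a cut-off. Over-reporting moves women from below it to above it, so a check that cannot see over-reporting does not establish what the Behavioral variables section says has to be established. This is not a detail deferred to a later document: the method is stated, and for continuous measures it does not answer the stated aim.

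**Working it through.** **The plan's own figure.** None exists. The article gives no target correlation, kappa or limits for this analysis, so there is nothing to reproduce.

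**Algebra.** Let true weekly minutes be T and logged minutes L = a + bT with b > 0. Then Pearson r(T, L) = 1 for every a and b, and Spearman rho = 1 for any increasing transformation. An added 10 minutes, or a factor of 1.3 or 1.5, leaves both at 1.00.

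**Illustration with random error.** From the article: the minimum pattern is 30 minutes twice a week, so 2 x 30 = 60 minutes a week. Assumed, not from the article: T is Normal with mean 50 and SD 25 minutes, cut off at zero; L = a + bT + error with SD 10 minutes; the criterion is reduced to at least 60 minutes a week, ignoring bouts, days and the six-week run. Simulated with 200,000 women:

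| Log | r | rho | Mean bias (min) | Met, true | Met, log | Log yes / true no | Log no / true yes | Kappa |
|---|---|---|---|---|---|---|---|---|
| Unbiased | 0.93 | 0.92 | 0 | 34% | 35% | 6.1% | 5.1% | 0.75 |
| T + 10 | 0.93 | 0.92 | +10 | 34% | 50% | 16.7% | 1.1% | 0.64 |
| 1.3 x T | 0.95 | 0.95 | +15 | 34% | 56% | 21.7% | 0.1% | 0.58 |
| 1.5 x T | 0.97 | 0.96 | +25 | 34% | 65% | 30.7% | 0.0% | 0.44 |

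The correlations do not fall as the log gets worse; under proportional over-reporting with fixed error they rise. The mean bias and the two discordant cells show the problem at once.

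**A second assumed distribution.** T lognormal with median 60 and log-SD 0.7, and L = bT with multiplicative error of log-SD 0.3. Pearson is 0.90 and Spearman 0.91 whether b is 1, 1.2 or 1.5, while the share meeting 60 minutes by log is 50%, 59% and 70% against a true 50%; kappa is 0.74, 0.70 and 0.57.

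**Sensitivity to the median.** In that model the true median sits exactly on the cut-off, where misclassification is large. The shares have closed forms: true = Phi(ln(median/60)/0.7) and log = Phi(ln(1.5 x median/60)/sqrt(0.7^2 + 0.3^2)), where the square root is 0.762. With an assumed median of 180:

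- true: Phi(1.099/0.7) = Phi(1.57) = 94%
- log: Phi(1.504/0.762) = Phi(1.97) = 98%

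So the inflation can be 20 percentage points or 4, depending on inputs the article does not supply. That correlations are blind to it does not depend on those inputs.

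**The case against.** **Cross-tabulation is also planned.** A reader might infer that agreement rests on correlations alone. It does not: the same sentence provides for cross-tabulation, depending on the variable. For a binary variable such as criterion met or not met, the margins and discordant cells of a two-by-two table show over-reporting directly, as the table above confirms. This part of the objection stands. What remains for the tables is only that no statistic is named that would summarise agreement or make the analyst read the disagreement by direction.

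**Steps and minutes share no unit.** Mean differences and limits of agreement between log and pedometer need a conversion that the article does not give. This also stands, and it is why the comparison has to be made on a common yes/no scale.

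**Self-reports cannot check one another.** A woman who inflates scale, IPAQ and log equally would show no difference between them. This stands too: such comparisons show consistency, not accuracy. The IPAQ is a poor comparator for a further reason. Table 2 schedules it at stage 1 and time 1, not at week 7. It covers the previous week rather than six weeks, and it is not confined to walking for exercise: eligible women, selected for not meeting the pattern, still have a median of 180.5 minutes a week.

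**The consequence for Phase II.** A reader might infer that the comparison of arms is biased. The documents do not support that. The illustration has no arms in it and shows an inflated proportion, not a distorted contrast; pedometer readings also enter the primary outcome. Nor does the article say that a high correlation would count as validation: its word is explore, and it sets no threshold.

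**Conclusion.** The point holds in a limited form. For continuous walking measures the only methods named are Pearson and Spearman correlations, which cannot detect constant or proportional over-reporting and so cannot deliver the concordance that the Phase I aim asks for. For categorical variables the planned tables can reveal it, but no agreement or asymmetry statistic is specified.

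The conclusion about correlations is algebraic and needs no assumption. The figures (34% becoming 50% to 65%, 50% becoming 70%, or 94% becoming 98%) are illustrations under assumed distributions, assumed over-reporting and a simplified criterion; they are not estimates for this trial. The issue concerns an exploratory Phase I aim, and no randomised analysis changes because of it. It is still worth correcting, because the protocol itself rests the use of logs for all women on this check.

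**What to change.** Amend the agreement sentence in Statistical analysis, Phase I, as follows.

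1. **Log against pedometer**, the comparison on which the use of logs depends. Among women with a pedometer, classify each day as walking or not by each instrument. The step threshold is an assumption to be fixed in advance and varied in sensitivity analysis. Report the cross-table with both discordant proportions, kappa, and sensitivity and specificity of the log against the pedometer. This assumes that daily pedometer counts can be retrieved.
2. **Week-7 ad hoc scale against the six-week log.** Report the mean difference with limits of agreement for minutes and for days, and kappa with both directions of disagreement for criterion met or not met. State that this shows consistency between two self-reports, not accuracy.
3. **Steps or distance against minutes.** Keep the correlations and label them as association.

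Do not add an IPAQ-versus-log comparison in Phase I, for the reasons of timing, period and construct given above.

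The cost is a few lines of text and some extra analysis of data already planned. Design, sample size and visits are unaffected.
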